## Abstract

**Background:**

The range of motion (RoM) of dorsiflexion (DF) plays an important role in human mobility, such as absorption of body weight during gait deceleration, jump landings, balance, and eccentric movements. This limitation can generate potentially damaging movements. This way, evaluating techniques for DF RoM increase could help improve immediate performance in such functional activities. This being the case, the objective of this study will be to verify the sum effect of different joint mobilization techniques for DF gain in persons practicing physical activities and its relationship with functional performance and balance.

**Methodology:**

This is a randomized, controlled, and blind clinical trial. Fifty-four (54) volunteers will be recruited, aged between 18 and 40 years, who have DF limitations. After checking eligibility criteria, the participants will be submitted to a physiotherapeutic evaluation. A researcher, blind to evaluation and treatment, will perform the randomization of patients in groups: (A) Joint Mobilization - *Mulligan* Concept and (B) Joint Mobilization - *Maitland* Method. All volunteers will be submitted by two blind evaluators for randomization and treatment groups. They will realize the initial evaluation (A0), immediately after techniques (A1) and after 3–4 days of the technique application (A2). A different researcher, blind for evaluation, will perform the treatment, according to the randomization group.

**Discussion:**

It is already known that DF RoM limitation can lead to compensatory and potentially damaging lower limb movements and that joint mobilizations are effective to treatment. However, there is no consensus whether the application of these techniques would also improve aspects of dynamic postural balance and performance in individuals practicing physical activity, and whether the sum of two joint mobilization techniques could enhance this effect.

**Trial registration:**

Brazilian Registry of Clinical Trials (ReBEC) RBR-93xv9t. Registered on 09 April 2020.

**Supplementary Information:**

The online version contains supplementary material available at 10.1186/s13063-021-05858-6.

## Background

Ankle dorsiflexion (DF) range of motion (RoM) plays an important role in absorbing body weight during gait deceleration, jump landings, and eccentric movements [1]. The arthro-kinematic movement of DF is performed by the anterior sliding of the tibia over the talus, in closed kinetic chain (CKC) and, in open kinetic chain (OKC), the posterior sliding of the talus in relation to the tibia [2]. In this manner, the expected DF RoM for this ankle movement is 45° in CKC and 22° in OKC [3]. Some studies suggest that lower values may be considered inadequate and associated with patterns of potentially predictive movements of lower limb injury [2, 4].

These movement patterns are related to physical activities that require a wide amplitude of DF, such as jumping, step-up, and step-down, since the RoM of normal DF collaborates in the load absorption imposed on the lower limb [2, 5, 6]. In conditions of CKC activities, DF limitation could difficult progression of the tibia over the talus, limit knee flexion, decrease absorption capacity of eccentric loads and lead to compensatory knee and hip movements in the frontal plan e[7].

Moreover, although the predisposing factors to injury are not totally conclusive, some studies show that DF RoM deficit perpetuates ankle instability [8–11]. So, to evaluate interventions that promote this movement is of great relevance for choosing the best techniques or combining different techniques, especially of the joint mobilization to improve ankle RoM and, consequently, to reduce risk of injuries, to treat and minimize compensations and overloads in lower limbs.

Another aspect considered by Vallandingham et al. [12] is associated with DF RoM relationship and dynamic postural balance. The authors observed that DF RoM deficit reduces balance. This being so, evaluating postural control in physically active volunteers with ankle dorsiflexion deficit will bring important information for us to understand its association with functional aspects of postural balance.

Physiotherapy has tools that restore RoM such as joint mobilization, often used for this purpose [10, 13]. Specifically for the gain of DF, two techniques are known and have already been studied. Mobilization with Movement (MWM) of the Mulligan Concept [11, 13, 14] is the first of them, in which the author of the technique reports that it is performed with movement close to functional in CKC [14]. According to the systematic review by Weerasekara et al. [15], this could bring immediate benefits with its application for DF RoM. However, this same study shows that there is no consensus on immediate improvement regarding other outcomes [15].

Another technique of joint mobilization which is widely used for DF improvement is the anteroposterior passive mobilization (AP) of the talus in relation to the tibia of the Maitland Method [16, 17]. According to some authors, there is no superiority when comparing techniques for improving RoM [18, 19], but no studies were found that evaluated the additional effect on DF RoM, postural balance, and functional performance when associated with these two techniques of joint mobilization in the same treatment.

The hypothesis of the present study is that the sum of the techniques may bring additional effects on ankle DF range of motion compared to the isolated Mulligan Concept technique; therefore, this study aims to evaluate the immediate and short-term additional effect of joint mobilization in relation to RoM, functional performance, and postural balance in the physically active population.

### Primary objective

To evaluate the immediate and short-term effect of the associated joint mobilization techniques, Mulligan concept and Maitland method, for the ankle joint, on range of motion.

### Secondary objective

To evaluate the immediate and short-term effect of the associated joint mobilization techniques, Mulligan concept and Maitland method, for the ankle joint, on functional performance and balance*.*

## Subjects and methods

### Study design

This study is a randomized, controlled, blind clinical trial with two parallel groups (Fig. 1). The study was approved by the Human Rights Ethics Committee under protocol number CAAE: 30660520.1.0000.5152 and registered in the Brazilian Registry of Clinical Trials (ReBEC) (registration number: RBR-93xv9t). Recruitment will begin in September 2020 with a probable end date of November 22, 2021, as a result of the pandemic in the country*.* According to the flowchart (Fig. 1), evaluations will be conducted pre-intervention (A0), post-intervention (A1), and 3–4 days after intervention (A2). Variables to be observed are: Amplitude of Motion of Dorsiflexion of ankle in 20 closed kinetic chain and open kinetic chain, postural balance, and functional performance.

**Fig. 1 Fig1:**
[figure not shown]
Flowchart of screening process and allocation of volunteers

### Participants and evaluators

Sample calculation was performed using a difference of means and standard deviation, based on closed kinetic chain range of motion, of similar works, being RoM of DF in CKC, primary outcome, performed through the lunge test (LT), and minimum clinically relevant difference of 3.8 degrees [20], with an estimated standard deviation of 4.4°, and considering ANOVA statistical test of repeated measurements. The protocol considered a 0.05 alpha level and an 80% statistical power, being a sample size of 23 volunteers per group. A possible sample loss (15%) was computed, a total of 54 volunteers was considered for randomization.

Eligibility criteria are as follows: men and women between the ages of 18 and 40 will be recruited who have a range of motion (RoM) in closed kinetic chain of less than 40°, verified by lunge test. If the volunteer has bilateral ankle dorsiflexion limitation, the most affected side will be considered for analysis and intervention.

Exclusion criteria are as follows: presenting musculoskeletal injury in the lower limb, rheumatic diseases, cardiovascular diseases, dizziness, vertigo or changes in the vestibular system, neuropathic problems, or any other alteration that could harm the volunteer’s health or compromise performance of tests.

These individuals will be recruited through posters on the campus of the Federal University of Uberlândia (UFU) and by dissemination on social media and local media (TV and radio). So as to increase adherence, especially in the post-intervention evaluations, the volunteers will receive orientation, after final evaluation (A2), as to perform the exercises to maintain or improve ankle RoM.

Research will be developed at the Laboratory of Evaluation in Biomechanics and Neurosciences (LABiN) of the Faculty of Physical Education and Physical Therapy of the Federal University of Uberlândia, Minas Gerais, Brazil.

### Procedures

All participants will receive a Free and Informed Consent Term approved by the Human Rights Ethics Committee under protocol number CAAE: 30660520.1.0000.5152.

Volunteers will be submitted to individual physiotherapeutic evaluation containing ankle range of motion, history of injuries and previous treatments, physical activities performed, history of other diseases and, if necessary, special tests for hip, knee, and ankle to exclude musculoskeletal changes in lower limbs, these being the eligibility criteria. After all eligible volunteers will be randomized into two groups by a researcher not involved with evaluation, intervention, and recruitment of volunteers.

Volunteers will be informed that they will receive physiotherapeutic intervention, but will not know the difference between treatment groups or study hypothesis. Randomization will be carried out by Microsoft Excell® RAND command and placed in a brown sealed envelope, listed sequentially to hide participants’ allocation. Randomization will be performed in blocks of volunteers. These will be distributed in two groups, where the number “0” generated by the program will be considered as “intervention A” group and number “1” will be considered as “intervention B” group.

Two researchers that are not involved with randomization and treatment processes, will perform the evaluations to determine the outcomes. So, the evaluators will be blind for randomization and treatments applied. After, other physiotherapists (researchers), who will not be involved in evaluations and randomization processes, will be responsible for applying treatment techniques, according to the randomization group.

All outcomes data will be stored in secured folders and will remain with the evaluators, responsible for tabulating in Excell® spreadsheets after the end of data collection, thereby guaranteeing blinding.

The researcher involved with the processing of the biomechanical signals and functional tests will be independent, not knowing the previous steps. After processing the signals, the researcher responsible for the randomization will distribute the volunteers in the referred groups, for later statistical analysis, which will be performed by an independent professional.

### Intervention/control

Sixty-four volunteers will be randomly allocated in 2 groups: (A) Articular Mobilization - *Mulligan* Concept; (B) Articular Mobilization - *Mulligan* Concept + Articular Mobilization - Maitland Method. Both groups will be submitted to intervention according to the techniques mentioned.

Intervention group A will be submitted to *Mulligan* mobilization technique—Mobilization with Movement (MWM)—where the physiotherapist will manually stabilize with continuous anteroposterior (AP) direction pressure on the talus and a belt will be passed around the distal region of the leg region of the volunteer e and waist of the therapist, performing a posteroanterior (PA) pressure with the belt, in this way, the mobilization of the talus and the mobilization of the leg, should be maintained throughout the entire movement. The technique will be performed during ankle dorsiflexion in closed kinetic chain (CKC) (Fig. 2A), with the volunteer positioned in semi-kneeling position, and then performing active dorsiflexion with weight bearing, and at the end of the active movement*,* the patient will be guided to perform a final pressure called overpressure.

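### The protocol gives two numbers to be randomised: 64 in the intervention section, 54 in the sample-size section and abstract

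*Protocol article*

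**What the plan says.** Three places in the protocol article give the planned number of volunteers.

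- **Participants and evaluators** (sample-size paragraph): the calculation ends in "being a sample size of 23 volunteers per group", and after a 15% allowance for loss "a total of 54 volunteers was considered for randomization".
- **Abstract, Methodology**: "Fifty-four (54) volunteers will be recruited".
- **Intervention/control**: "Sixty-four volunteers will be randomly allocated in 2 groups".

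The calculation rests on a "minimum clinically relevant difference of 3.8 degrees" for dorsiflexion in the lunge test, "with an estimated standard deviation of 4.4" degrees, and this statement on error rates: "The protocol considered a 0.05 alpha level and an 80% statistical power". It names repeated-measures ANOVA as the test but gives no within-subject correlation.

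**The concern.** The sample-size paragraph and the intervention section both describe the number randomised to the same two groups, and they differ by 10. The abstract speaks of recruitment rather than randomisation, but this does not reconcile them, since 64 people cannot be randomised from 54 recruited. The intervention section refers to random allocation, so 64 cannot be read as a number screened. No text presents it as a revised target or a different population.

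The number to be randomised determines how many sequential envelopes are prepared, when recruitment stops and what power the trial can claim. With two targets, stopping at either one agrees with one section and departs from another. A final report with 54 could look like a shortfall of 10, and a report with 64 like an unexplained overrun. Volunteers beyond 54 would have no stated sample-size justification. The Intervention/control section opens the trial to audit by the ethics committee, but enrolment cannot be audited against two targets.

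**Working it through.** **Inputs** (all from Participants and evaluators): difference 3.8 degrees, SD 4.4 degrees, alpha 0.05, power 80%, loss 15%. Two groups of equal size. Sidedness is not stated, so two-sided is assumed.

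**Step 1: the stated 23 per group.** Standardised difference d = 3.8/4.4 = 0.864.

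- Normal approximation: n per group = 2 × (1.960 + 0.842)² × 4.4²/3.8² ≈ 21.05, rounded up to 22.
- Two-sample t-test (noncentral t): 22.05, rounded up to **23**. This reproduces the protocol's figure.
- One-sided alpha would give 17 (normal) or 18 (t), which does not match, so two-sided is the reading that fits.

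**Step 2: the stated total of 54.** Two groups of 23 make 46 evaluable.

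| Inflation for 15% loss | Calculation | Total |
|---|---|---|
| Divide the total by 0.85 | 46/0.85 = 54.1 | 54, or 55 if rounded up |
| Divide per group by 0.85 | 23/0.85 = 27.06, rounded up to 28 | 56 |
| Multiply the total by 1.15 | 46 × 1.15 = 52.9 | 53 |
| Multiply per group by 1.15 | 23 × 1.15 = 26.45, rounded up to 27 | 54 |

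The range is 53 to 56, so 54 is consistent with the inputs.

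**Step 3: can 64 be reached?**

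- Excess over the stated total: 64 − 54 = 10, and 10/54 = 18.5%.
- Evaluable after 15% loss: 54 × 0.85 = 45.9, which matches the required 46. By contrast 64 × 0.85 = 54.4, about 8 more than required.
- Loss needed to go from 64 to 46: 1 − 46/64 = 28.1%, almost twice the stated 15%.
- Applying the 15% a second time gives 54/0.85 = 63.5, which rounds up to 64. This is arithmetically possible, but the document does not say it was done. A slip in one word would produce the same text.

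**Step 4: what each number means for power** (two-sample t-test, d = 0.864, two-sided 0.05).

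| Evaluable per group | Corresponds to | Power |
|---|---|---|
| 23 | 54 randomised, 15% lost | 81.7% |
| 27 | 54 with no loss, or 64 with 15% lost | 87.6% |
| 32 | 64 with no loss | 92.5% |

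The repeated-measures calculation cannot be checked directly without the within-subject correlation. The two-sample calculation already returns 23, and the conflict between 54 and 64 does not depend on which test was used.

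**The case against.** The best defence is that this is a one-word slip with little consequence. Only one place derives a sample size, it yields 54, and the abstract agrees. The 64 appears once, without derivation, in a section about the interventions. A careful reader can see which figure the reasoning supports, and neither figure weakens the design. The allocation flowchart (Fig. 1) is not reproduced in the text at hand and might show which number was intended.

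A data-driven choice between 54 and 64 is also unlikely. Under Procedures, the evaluators are blind to allocation, outcomes are tabulated after data collection ends, group membership is attached only after signal processing, and an independent professional does the analysis. No interim look is described.

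Much of this stands. The concern should not be read as suggesting that recruitment would be extended on sight of results, and the double-inflation explanation is conjecture. But blinding does not supply a stopping number, and a flowchart showing either figure would still leave the prose in conflict. The number to be randomised is a figure the trial is run and reported against, so a slip there needs correcting even when its likely origin is innocent.

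**Conclusion.** The point holds. The protocol states two values for the number randomised, 54 and 64, a difference of 10 volunteers or 18.5% of the derived total. The document's own inputs support 54 (53 to 56 by convention) and do not produce 64. This rests on two-sided alpha and equal allocation. Neither assumption is spelled out, but a two-sided test reproduces the stated 23 per group, and that single per-group figure implies equal groups.

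The fault is an unreconciled enrolment target, not a lack of power. It must be corrected because the end of recruitment and the judgement of whether the trial met its target both depend on this number.

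**What to change.** In Intervention/control, replace sixty-four with fifty-four, in agreement with the sample-size paragraph and the abstract. If a per-group number is added, 27 follows from equal allocation of 54; the document does not state it.

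If 64 is the real target, leave it there, rewrite the sample-size paragraph so that its assumptions lead to 64, and change the abstract to match.

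In either case, state that recruitment stops at that single number and check that the flowchart agrees. The Trial status section puts the first evaluation in January 2021 and expects data collection to end in November 2021. If enrolment has already passed 54 or closed, the correction should be dated, and the report should say which target was in force and how many were randomised.

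The cost is a one-line protocol correction, or a short rewrite of one paragraph if 64 is kept. Correcting to 54 needs no additional participants and no change to the analysis.

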**Fig. 2 Fig2:**
[figure not shown]
**A**
*Mulligan* mobilization technique - Mobilization with Movement (MWM) and **B** Maitland method technique

Intervention will be performed in 3 series of 10 repetitions. In addition, the volunteer will be guided to perform self-mobilization by performing oscillatory movements at the end of DF with CKC, in 3 series of 10 repetitions per day, aiming at gaining an ankle DF during 3 days [14, 19].

Intervention group B will also be submitted to technique cited in group A plus Maitland method technique, which will be applied after intervention A, in grade IV, with volunteer in dorsal decubitus, and foot out of stretcher. Mobilization will occur through a passive oscillatory pressure in AP direction in talus, for 5 series of 1 min [19, 21] (Fig. 2B). All techniques will be performed by a physiotherapist trained and experienced in clinical applicability of both techniques.

All stages of the clinical trial, randomization, blinding, and data collection are available to be audited by the institution’s Human Rights Ethics Committee, and the researchers are responsible for submitting six-monthly reports on the progress of the work.

### Outcome measurements

Three outcome measurements will be evaluated, 2–3 days before intervention application (A0), after immediate intervention (A1), and 3–4 days after intervention (A2).

#### Primary outcome

The primary outcome corresponds to DF ankle range of motion in CKC measured through lunge test (LT).

#### Secondary outcome

Secondary outcome corresponds to passive ankle DF measured in OKC by means of a goniometer, Postural Control which will be evaluated through the oscillation of CoP during the evaluation of Y balance test, which will be carried out on force platform, with functional performance evaluated through Y balance test (YBT) and triple hop test (THT) and, satisfaction evaluated through Medrisk satisfaction questionnaire [22].

Each result measurement is described below:

##### Range of motion

DF RoM will be measured in CKC performed by LT, this test being of high reliability for measurement of DF (ICC = 0.98) [9]. To this end, a smartphone and an application will be used for the acquisition of measurements (Clinometer^Ⓡ^), this application having already been validated [23].

Lunge test will be performed with participant barefoot and with weight bearing on member evaluated (Fig. 3A). A 50-cm line will be fixed on the ground and a continuous 60-cm line will be demarcated on the wall to perform the test [3]. Cell phone device will be positioned 15 cm away from anterior tibial tuberosity [3]. Participants will be positioned with their feet along the line on the ground and then will be asked to move maximum DF, thereby bringing the knee closer to a vertical line drawn on the wall, without the foot moving from the ground (Fig. 3A). Once maximum DF is reached, the examiner will position the inclinometer on reference marked on the volunteer’s leg. The angle (in degrees) of DF and distance (in cm) from the tip of the 1st toe to the wall will be computed. The participant will return to the initial position. The procedure will be repeated 3 times and average calculated for later analysis [4].

**Fig. 3 Fig3:**
[figure not shown]
**A** Evaluation of ankle DF RoM during lunge test. **B** Evaluation of ankle DF RoM during goniometry

RoM will also be measured in OKC by means of goniometry, a method validated by Petherick et al. in 1988 [24]. The participant will remain in a ventral decubitus position, knee positioned at 90°, and asked to perform ankle DF movement and then evaluator will help to complete maximum DF range passively. The goniometer will be positioned on the lateral malleolus with its central axis, fixed arm directed towards lateral epicondyle of knee, and mobile axis will be directed towards the 5th metatarsal (Fig. 3B). This procedure will be repeated 3 times and mean calculated for later analysis [24].

##### Postural Control

Postural control will be evaluated during the execution of YBT using the force platform.

Postural oscillation will be evaluated through analysis of the center of pressure (CoP) displacement with data obtained during the execution of YBT, performed during use of force platform (EMGSystem do Brasil® São José dos Campos, SP), with sampling frequency being 500 Hz. Force signals obtained (Fx, Fy, and Fz) and the moments of these forces (Mx, My and Mz), will be used to determine CoP oscillation, with the direction of CoP oscillation being considered, [+x]- anterior; [+y]- right and [+z]- upper directions will also be used.

Collecting environment will have controlled temperature and noise level minimizing interference in postural control. Participants will be previously oriented as to positions that should be performed during data collection. The volunteer must be initially positioned with face facing the posterior direction of platform (−Fy).

During the execution of YBT, the volunteer will be tested in *unipodal* support under the force platform. Participants will be positioned with their foot to be evaluated at intersections of lines, formed by previous, posterior-medial, and posterior-lateral directions marked on the force platform. Participants will be verbally instructed to perform maximum reaches in three directions, with contralateral limbs, with upper limbs positioned at waist level [25] (Fig. 4).

